### 3.4. Sample Size

An a priori sample size calculation was performed based on the BMI z-score. For the preschool-based component, the expected difference between the intervention and control condition was 0.10 BMI points [70]. Given a power of 0.90 and α < 0.05, a sample of 115 children in each group was required to detect this difference. Correcting for the potential nesting of effects within a preschool, considering an intraclass correlation of 0.0006, which corresponds to a design effect of 1.23, a total of 142 children should be included. Taking into account an attrition rate of 20%, 171 children should be included in each study group, resulting in 342 children.

For the family-based component, the expected difference between the intervention and control group is 0.30 BMI z-points [70]. Taking into account a power of 0.90 and α < 0.05, a sample of 38 families is required. Adjusting for an attrition rate of 30% a total of 50 families is the target for inclusion in the family-based component.

Recruitment for this study was done between January and April 2017 for the intervention group and between January and July 2017 for the control group. A flow diagram of participation is shown in Figure 2. Parents of 23.9% of the children attending intervention preschools agreed to participate in the preschool component, 41.0% of these parents also agreed to participate in the family-based component, and 26.7% of parents of children in the control preschools agreed to participate. Of the preschool teachers, 91.4% from the intervention preschools and 65.0% from the control preschools agreed to participate.

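### The attrition allowances multiply by (1 + rate) instead of dividing by (1 − rate), so the targets of 171 children per group and 50 families fall slightly short of the required 142 and 38

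*Protocol article*

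**What the plan says.** All the figures are in section 3.4 (Sample Size) of the protocol article.

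- **Preschool component.** For power and significance level it states "Given a power of 0.90 and α < 0.05", and "a sample of 115 children in each group was required to detect this difference". The clustering adjustment is given as "considering an intraclass correlation of 0.0006, which corresponds to a design effect of 1.23", after which "a total of 142 children should be included". The attrition step reads: "Taking into account an attrition rate of 20%, 171 children should be included in each study group, resulting in 342 children".
- **Family component.** With the same power and significance level and a difference of 0.30 BMI z-points, 38 families are required. Then: "Adjusting for an attrition rate of 30% a total of 50 families is the target for inclusion in the family-based component".
- **Recalculation.** The section goes on to report that the planned size was not reached. With 99 intervention and 92 control children it gives a detectable difference of 0.19 BMI z-points, plus detectable differences for physical activity and diet. It says that these rest on the assumptions used in the a priori calculation.

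**The concern.** An attrition allowance should leave the required number of participants after the expected losses. If a fraction d is lost, enrolment must be n/(1 − d). Adding d × n to the requirement falls short, because the loss applies to the larger enrolled number and not to the required number.

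If the targets were built the second way, the article's own inputs do not deliver the 90% power it states, for children or for families. The question also carries over to the recalculation. Its detectable differences, which the article calls attainable, are tied to 99 and 92 children with no visible allowance for later loss.

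**Working it through.** **Inputs, all from section 3.4:** 115 children per group before clustering; design effect 1.23; 142 after clustering; 20% attrition and 171 per group; 38 families; 30% attrition and 50 families; power 0.90, α 0.05. The 115, 1.23 and 38 are taken as stated. No standard deviation is printed, so 115 and 38 cannot be rebuilt, but the attrition check does not need them to be.

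**Step 1. Reproduce the plan's figures.**
- Clustering: 115 × 1.23 = 141.45, rounded up to 142. This shows that 142 is per group, although it is worded as a total.
- Children, n × (1 + d): 142 × 1.20 = 170.4, rounded up to 171. Matches.
- Families, n × (1 + d): 38 × 1.30 = 49.4, rounded up to 50. Matches.

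**Step 2. Apply n/(1 − d).**
- Children: 142/0.80 = 177.5, so 178 per group and 356 in all. From the unrounded 141.45: 176.8, so 177 per group and 354 in all.
- Families: 38/0.70 = 54.3, so 55.

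Rounding does not explain the gap from 171 and 50.

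**Step 3. What the stated targets leave.**

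| | Target | Retained at stated attrition | Required | Attrition actually covered |
|---|---|---|---|---|
| Children per group | 171 | 171 × 0.80 = 136.8 | 142 | 1 − 142/171 = 17.0% |
| Families | 50 | 50 × 0.70 = 35 | 38 | 1 − 38/50 = 24.0% |

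**Step 4. Power after attrition.** With a normal approximation, power depends only on the ratio of retained to required n, so the missing standard deviation cancels. For a two-sided 0.05 test (an assumption, since sidedness is not stated), 1.96 + 1.2816 = 3.2415 and power = Φ(3.2415 × √(retained/required) − 1.96).
- Children: Φ(3.2415 × √(136.8/142) − 1.96) = Φ(1.222) = 88.9%.
- Families: Φ(3.2415 × √(35/38) − 1.96) = Φ(1.151) = 87.5%.

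A one-sided 0.05 test (1.645 + 1.2816 = 2.926) gives 89.0% and 87.8%. The family result is the same whether 38 is per group or in total.

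**Step 5. Can the 0.19 be traced?** This needs a standard deviation back-solved from section 3.4: SD = difference/3.2415 × √(n/2), and detectable difference = 3.2415 × SD × √(1/99 + 1/92), where the root is 0.1448. Attrition of 20% multiplies the result by 1/√0.8 = 1.118, and the design effect multiplies it by √1.23 = 1.109.

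| Source of SD | SD | Neither | Design effect only | Attrition only | Both |
|---|---|---|---|---|---|
| Difference 0.10, 115 per group | 0.234 | 0.110 | 0.122 | 0.123 | 0.136 |
| Difference 0.30, 38 per group | 0.403 | 0.189 | 0.210 | 0.212 | 0.235 |
| Difference 0.30, 38 in total (19 per group) | 0.285 | 0.134 | 0.149 | 0.150 | 0.166 |

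Only one cell matches 0.19: the family inputs with 38 read as per group, and with neither allowance applied.

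**The case against.** The strongest case on the other side concerns weight, not arithmetic. The loss is 1.1 power points for children and 2.5 for families, and the children's loss is small beside the uncertainty in any assumed attrition rate. The target was also overtaken by events: 99 + 92 = 191 children were enrolled against 342, a gap of 151 that the article discloses. Beside that, the 14 children between 342 and 356 affect no analysis or conclusion. All of this stands, and it is why the point is minor. It does not make the printed targets follow from the printed inputs.

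A reader might go further and infer that the recalculation dropped attrition altogether, so that 0.19 should read 0.21. The article does not support stating that as fact.
- It says that the a priori assumptions were kept, which read literally includes the 20%.
- No standard deviation is given. The single match in step 5 relies on one back-solved from the family inputs, under one reading of 38.
- That same match omits the design effect as well, so 0.21 would not be the fully corrected value either; it would be about 0.235 with both allowances.
- Section 3.3 plans linear mixed models for repeated measurements, and section 3 (Data Collection) has two follow-ups. A child who misses the final visit can still contribute, so dividing by √0.8 gives an upper bound.

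What remains is a question for the sponsor: the differences are tied to 99 and 92, and no allowance is visible.

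**Conclusion.** The attrition step in section 3.4 is wrong as written, in both components. The targets of 171 per group and 50 families leave 136.8 and 35 at the stated attrition, against 142 and 38 required. They fall short of the proper targets by 7 children per group (14 in all; 6 and 12 from the unrounded 141.45) and by 5 families. Power is about 89% and 87.5% instead of 90%, given a normal approximation, a two-sided 0.05 test, and 115, 1.23 and 38 as stated.

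Severity is minor, because actual enrolment, and not this slip, determines the power achieved.

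For the recalculated detectable differences, the position is unresolved. If attrition was not applied, each figure computed on 99 and 92 rises by up to about 12%, so 0.19 becomes at most about 0.21 for attrition alone. That is an inference and an upper bound.

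**What to change.** 1. Restate the targets as 178 children per group (356 in all; 177 per group from the unrounded 141.45) and 55 families. Alternatively, keep 171 and 50 and state that they cover 17% and 24% attrition.
2. State that 142 is per group.
3. State whether the detectable differences based on 99 and 92 include the 20% attrition and the design effect, and give the standard deviations used. If attrition was not included, restate the differences for retained children, noting that the factor 1/√0.8 is an upper bound under the planned mixed model.

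The cost is corrected text and one recalculation. Recruitment is closed, and no participants, measurements or design changes are needed.

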As the a priori calculated sample size was not reached, an additional power calculation was conducted. Based on the sample size (intervention *N* = 99; control *N* = 92), a difference of 0.19 BMI z- points can be detected, which seems attainable based on the available evidence [37,70]. The calculations are based on the same assumptions of the a priori sample size calculation. In addition, an increase of 1.44% of time in moderate-to-vigorous physical activity (MVPA) per day (corresponding to 8.91 min per day), 0.33 instances of fruit consumption per day, 0.26 instances of vegetable consumption per day, and 0.57 instances of water consumption per day can be detected. A decrease of 0.52 instances of sugar-sweetened beverages consumption per day and 0.61 instances of snack consumption per day can be detected. These differences also seem attainable based on the available evidence [59,71].

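### The recalculated detectable difference of 0.19 BMI z-points does not follow from the preschool calculation's assumptions and is nearly twice the 0.10 on which that component was planned

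*Protocol article*

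**What the plan says.** All of this stands in section 3.4 (Sample Size) of the protocol article.

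- **Preschool component.** "For the preschool-based component, the expected difference between the intervention and control condition was 0.10 BMI points". "Given a power of 0.90 and α < 0.05, a sample of 115 children in each group was required to detect this difference". Then clustering: "considering an intraclass correlation of 0.0006, which corresponds to a design effect of 1.23, a total of 142 children should be included". A 20% attrition allowance takes 142 to 171 per group.
- **Family component.** The expected difference is 0.30 BMI z-points. At the same power and alpha, "a sample of 38 families is required", and after a 30% attrition allowance "a total of 50 families is the target for inclusion in the family-based component". The step introduced for the preschool component by "Correcting for the potential nesting of effects within a preschool" has no counterpart here.
- **Uptake.** 41.0% of the consenting intervention parents also joined the family component.
- **After the shortfall.** For 99 intervention and 92 control children, "a difference of 0.19 BMI z- points can be detected, which seems attainable based on the available evidence [37,70". The article adds that the assumptions of the a priori calculation were carried over. No recalculated BMI z-score figure is given for the family component.

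No standard deviation appears in either calculation or in the recalculation.

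**The concern.** The recalculation is there to reassure the reader that the smaller trial is still adequate. It does so by quoting a detectable difference of 0.19 and calling it attainable. But the component to which the 99 v 92 comparison belongs was planned on 0.10. A trial that can detect only 0.19 with 90% power is not adequately powered for an expected 0.10.

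The sample also fell too little to explain the change. Analysable numbers drop from 115 per group to 99 and 92, which should raise the detectable difference by about a tenth, not by 90%. Some assumption must have changed, although the text says none did.

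At stake is how a null BMI z-score result will be read. If the stated figure is taken at face value, such a result looks like evidence against an effect of a plausible size, when the effect actually expected may have had well under 90% power.

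**Working it through.** **Inputs (section 3.4).** Preschool: difference 0.10, 115 per group, power 0.90, alpha 0.05, design effect (DE) 1.23, intraclass correlation (ICC) 0.0006, attrition 20%. Family: 0.30, 38 families, attrition 30%. Achieved: 99 and 92. Assumed: two-sided test, normal approximation, 0.10 read as z-points because the section says the calculation is based on the BMI z-score, and 38 read as per group unless noted.

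**1. The plan's a priori steps.** 115 × 1.23 = 141.5, so 142. 142 × 1.20 = 170.4, so 171. 38 × 1.30 = 49.4, so 50. All match.

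**2. Can 0.19 come from the preschool inputs?** At fixed SD, alpha and power, the detectable difference scales with √(1/a + 1/b), so no SD is needed.
- √(2/115) = 0.1319; √(1/99 + 1/92) = 0.1448.
- Unadjusted: 0.10 × 0.1448/0.1319 = **0.110**.
- With DE 1.23: 0.110 × √1.23 = **0.122**.
- With 20% attrition (79.2 v 73.6): 0.110/√0.8 = **0.123**.
- With both: **0.136**.

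None is near 0.19.

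**3. Can it come from the family inputs?** With 38 per group, √(2/38) = 0.2294.
- Unadjusted: 0.30 × 0.1448/0.2294 = **0.189**, which reproduces 0.19.
- With DE 1.23: **0.210**. With 20% attrition: **0.212**. With both: **0.235**.
- With 38 as the total (19 per group), the results run from 0.134 unadjusted to 0.166 with both, so 0.19 is not reached.

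**4. Implied SDs.** SD = difference × √(n/2)/(1.960 + 1.282).
- Preschool: 0.10 × √57.5/3.2415 = 0.234.
- Family: 0.30 × √19/3.2415 = 0.403.

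The two calculations thus imply different SDs for one outcome. With a single SD, tripling the difference would cut 115 to 115/9, about 13 per group, not 38.

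**5. Power for the planned 0.10.** Power = Φ(0.10/[SD × √(DE × (1/a + 1/b))] − 1.960).

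| | 99 v 92, no adjustment | 79.2 v 73.6, DE 1.23 |
|---|---|---|
| SD 0.234 | 84% | 66% |
| SD 0.403 | 40% | 28% |

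**6. ICC against design effect.** DE = 1 + (m − 1) × ICC. For 1.23 at ICC 0.0006, m = 1 + 0.23/0.0006, about 384 children per preschool. The achieved means are 99/12 = 8.25 and 92/9 = 10.2, which give DE of about 1.004 and 1.006. The two stated inputs are incompatible.

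**7. Family component.** 0.41 × 99 is about 41 recruited; 41 × 0.7 = 28.7 retained, against 92 × 0.8 = 73.6 controls. Power for 0.30 at SD 0.403 is 92% with DE 1, 91% with DE 1.05 and 86% with DE 1.23. If 38 is a total (SD 0.285), it is at least 99%. Against a comparator of only 28.7, it is 80% (DE 1) or 72% (DE 1.23).

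**The case against.** **The SD is not published, so these figures are back-solved.** True, and the full protocol may state it. But the scaling in steps 2 and 3 needs no SD. It needs only that the assumptions were unchanged, as the article says. An SD chosen to make 0.19 come out with the design effect included (about 0.365) matches neither a priori calculation.

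**99 v 92 is the right comparison for the preschool component.** This stands. Every consenting intervention child receives the preschool component, and some families receive the family component as well. A reader might infer that 0.19 is an improper pooling that belongs to neither component. The article does not support that: it compares intervention with control and names no preschool-only contrast. The fault lies in the figure, not in the groups compared.

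**The family component may still have its 90%.** This also stands. It is tempting to conclude that the power has been lost, because uptake was below target and nesting was ignored. But at 28.7 families against all retained controls, power stays above 90% unless the design effect is well above 1.05. The value 1.23 conflicts with the ICC printed beside it. Section 2.5 describes further recruitment to the family component, including from other preschools, with no count in the text shown. At DE 1.23, 35 retained families would already give 90%. The text also leaves open whether 38 is per group or total, and which comparator applies.

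**Conclusion.** The point holds for the stated figure. The 0.19 is not what the preschool assumptions give at 99 v 92 (0.11 to 0.14), and it is nearly twice the difference that the component was planned to detect. It agrees with the family-implied SD only when the design effect and attrition are both left out; with them it is about 0.235. Power for 0.10 is 66% to 84% at the SD implied by the preschool calculation and 28% to 40% at the SD implied by the family calculation. In no case is it 90%. Calling 0.19 attainable therefore conflicts with the plan's own expectation for this component.

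For the family component, what is established is narrower: no nesting correction is shown, no recalculation is reported, and initial uptake of about 41 was below 50. A fall below 90% power is possible, with 86% to 92% the range if 38 is per group, all retained controls are used and no later families are added. It is not demonstrated.

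The conclusions assume a two-sided test, a normal approximation and 0.10 in z-score units. The uptake of 41 applies the 41.0% to 99; the exact denominator is not in the text shown.

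**What to change.** In section 3.4:

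1. State the SD of the BMI z-score used and its source, and use one value throughout or explain why the two components differ. Say whether 0.10 is in z-score units and whether 38 families is per group or in total.
2. Reconcile the ICC of 0.0006 with the design effect of 1.23, giving the cluster size used.
3. Restate the detectable difference for the preschool component (99 v 92) and for family v control. Use enrolled numbers, including any families who joined later, the plan's own attrition rates (20% and 30%) and the one reconciled design effect for both. Report power for 0.10 and 0.30 alongside.
4. Withdraw the attainability statement wherever the detectable difference exceeds the planned 0.10, and say plainly that a null BMI z-score result will not exclude the expected effect.

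No further recruitment or change of design or analysis is needed. The cost is a few restated figures, which will be less favourable than those now printed.

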Regarding nutrition, the strategies focused on increasing the variety and availability of fruit and vegetables during snack time and providing general nutrition-related materials [17]. A local greengrocer supplied unfamiliar fruits or vegetables (e.g., cherries, raspberries, avocado, celery) to increase the variety of fruits and vegetables. This supplemented the fruits that the children would bring to the preschool from home and was available every day. The supplied fruits or vegetables were similar during the two weeks to increase repeated exposure of the children to each new product [45,60]. The general nutrition-related materials were part of the general box, with play materials, and were matched with nutrition-related cards. Materials included a water tap, fruit and vegetable toys, nutrition-related story books, and materials to involve children in preparing foods. Preschool teachers could also express the need for specific nutrition-related materials (e.g., a blender) to supplement the general materials that were delivered.

The political environment was defined as ‘the institutional policies related to nutrition and PA’ [50]. The strategies of SuperFIT focused on updating the nutrition policy and initiating the development of a PA policy, as this was not yet in place. Particular subjects of interest for the nutrition policy were the availability of water and healthy treats and preschool teacher practices. The PA policy was formulated to provide recommendations on the amount of time at childcare that should be spent active. It was intended to provide guidelines around safe play, particularly in a physical education room.

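### Detectable differences for activity and diet are published with no clustering value of their own, and the one they appear to borrow (ICC 0.0006, design effect 1.23) contradicts itself

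*Protocol article*

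**What the plan says.** Section 3.4 of the protocol article opens with a calculation for one outcome: "An a priori sample size calculation was performed based on the BMI z-score". It continues: "Given a power of 0.90 and α < 0.05, a sample of 115 children in each group was required to detect this difference". Clustering enters once: "considering an intraclass correlation of 0.0006, which corresponds to a design effect of 1.23, a total of 142 children should be included".

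The second half of the section reports that the target was missed and recalculates with 99 intervention and 92 control children, giving a detectable difference of 0.19 BMI z-points. It then says: "The calculations are based on the same assumptions of the a priori sample size calculation". The behavioural figures come next, as an addition: "an increase of 1.44% of time in moderate-to-vigorous physical activity (MVPA) per day (corresponding to 8.91 min per day"), 0.33 fruit, 0.26 vegetable and 0.57 water instances per day as increases, and 0.52 sugar-sweetened beverage and 0.61 snack instances per day as decreases. The section calls these differences attainable on the available evidence. It gives no ICC, design effect or standard deviation for any of them.

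The Abstract and the Introduction list physical activity and dietary intake as primary outcomes beside the BMI z-score. Section 2.3.1 describes how the intervention reaches these behaviours through the preschool: teacher training and coaching, play materials, policy, and supplied fruit and vegetables ("This supplemented the fruits that the children would bring to the preschool from home and was available every day").

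**The concern.** A detectable difference in a clustered design depends on the ICC of the outcome concerned. A value chosen for BMI z-score need not suit activity or diet, which children at one preschool partly share through their teachers and play space. The trial's rationale is that the preschool shapes these behaviours, so using the BMI z-score's value for them needs a reason, and none is given.

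The borrowed assumption also has two incompatible parts. A reader cannot tell whether the behavioural figures contain almost no clustering allowance (ICC 0.0006) or a moderate one (design effect 1.23).

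At stake is the reading of a null result. If the trial finds no difference in MVPA or snacks, the published figures invite the conclusion that an effect of that size was excluded with 90% power. That conclusion may not be warranted.

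**Working it through.** **Inputs.** From section 3.4: power 0.90, α 0.05 (taken as two-sided, which the article does not state), ICC 0.0006, design effect (DE) 1.23, 99 and 92 children. From section 2.5: 12 and 9 preschools, hence 99/12 = 8.25 and 92/9 = 10.2 children per preschool (191/21 = 9.1 overall). Behavioural ICCs are not in the document; 0.01 to 0.10 is an assumed range.

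**The plan's own figures.** 115 × 1.23 = 141.45, rounded up to 142, so 1.23 is the value actually applied a priori. The two MVPA figures agree with each other: 8.91/0.0144 = 619 minutes, or 10.3 hours of measured day. The behavioural differences themselves cannot be reproduced, because no standard deviation is given.

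**Consistency of 0.0006 and 1.23.** With DE = 1 + (m − 1) × ICC, a DE of 1.23 at ICC 0.0006 needs m = 1 + 0.23/0.0006 ≈ 384 children per preschool. For the realised clusters, weighting the arms by 1/99 and 1/92:

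DE = 1 + [7.25/99 + 9.22/92] / [1/99 + 1/92] × ICC = 1 + 8.27 × ICC

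ICC 0.0006 therefore gives DE 1.005, and DE 1.23 corresponds to ICC 0.23/8.27 = 0.028.

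**Effect of a larger behavioural ICC.** Let DE0 be the design effect behind the published figures. The detectable difference scales by r = √(DE/DE0), and power at the published difference is Φ(3.2415/r − 1.960), where 3.2415 = 1.960 + 1.2816.

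| Assumed ICC | DE | r, DE0 = 1.005 | MVPA min/day | Power | r, DE0 = 1.23 | MVPA min/day | Power |
|---|---|---|---|---|---|---|---|
| 0.01 | 1.083 | 1.038 | 9.25 | 88% | 0.938 | 8.36 | 93% |
| 0.02 | 1.165 | 1.077 | 9.60 | 85% | 0.973 | 8.67 | 91% |
| 0.05 | 1.414 | 1.186 | 10.57 | 78% | 1.072 | 9.55 | 86% |
| 0.10 | 1.827 | 1.348 | 12.01 | 67% | 1.219 | 10.86 | 76% |

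The same factors apply to diet. With DE0 = 1.005, fruit 0.33 becomes 0.39 at ICC 0.05 and 0.44 at 0.10; snacks 0.61 becomes 0.72 and 0.82.

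The table changes only the clustering term. If the published figures assume that all 191 children are analysed, the 20% attrition in section 3.4 lowers power further.

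**Which DE0 was used?** The 0.19 for BMI z-score gives a hint, but not an answer. With √(1/99 + 1/92) = 0.1448, the detectable difference is 3.2415 × 0.1448 × SD × √DE.

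- SD 0.403, implied by the family calculation if 38 families means 38 per group: 0.19 at DE 1.005 and 0.21 at DE 1.23.
- SD 0.285, if 38 is the total: about 0.13 at DE 1.005.
- SD 0.234, implied by 0.10 and 115 per group: 0.11 at DE 1.005 and 0.12 at DE 1.23.

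Of these, only the first at DE 1.005 returns 0.19. It relies on a standard deviation from another calculation and on a reading of 38 that the text does not confirm.

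**The case against.** A reader might infer that the activity and diet figures are simply too favourable. The documents do not support that as a fact, for four reasons.

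First, the carry-over is an inference. The sentence on shared assumptions follows the BMI z-score figure and precedes the behavioural ones. It remains the natural reading, since the sentence is in the plural and no other assumption is offered.

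Second, if 1.23 was kept, the allowance equals an ICC of about 0.028, and the figures are conservative for any behaviour that clusters less than that. This stands, and it is why both cases are shown.

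Third, the shared exposures are weaker evidence of clustering than they look. The ICC reflects differences between preschools within an arm. Fruit from one greengrocer and policy within one childcare organisation mainly shift the arm mean. Preschool is half-day (section 2.2), diet is also recalled at home (section 3.1.2), and accelerometers are worn through waking hours (section 3.1.3), all of which dilute clustering. This stands too. Teachers and play space remain plausible sources of between-preschool variation, but the size is unknown.

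Fourth, section 3.3 specifies linear mixed models with child and preschool levels, so the analysis itself will reflect the actual clustering. That is correct, and the point does not touch the validity of the effect estimates. It concerns the published power figures. A condensed article may leave standard deviations to a fuller document, but here it prints specific detectable differences and draws a conclusion about attainability from them.

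**Conclusion.** The point holds in a conditional form. The article publishes detectable differences for six activity and diet measures without a clustering value for any of them. The only value it offers was set for BMI z-score, and its two parts disagree by a factor of about 46 in ICC (0.028/0.0006).

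Whether the figures are optimistic depends on two unknowns: which design effect was used, and the true behavioural ICC. The break-even ICC is 0.0006 in one case and about 0.028 in the other. Over an assumed ICC of 0.01 to 0.10, power at the stated differences runs from 88% down to 67% in the first case and from 93% down to 76% in the second. This assumes two-sided testing, even cluster sizes within each arm and no further attrition.

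The match of 0.19 with a design effect near 1 might be taken as proof that clustering was ignored. It is suggestive at most, because it needs 38 families to mean 38 per group, and it concerns BMI z-score rather than the behaviours.

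**What to change.** In section 3.4:

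- State which design effect underlies the second set of calculations, and whether the behavioural figures share it.
- Reconcile ICC 0.0006 with design effect 1.23, giving the cluster size assumed.
- Restate each behavioural detectable difference at the actual cluster sizes (about 8 and 10 children per preschool) over an ICC range of 0.01 to 0.10, with the stated 20% attrition and the standard deviation used.

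An ICC for each behaviour, estimated from the baseline data with group in the model, could be added as support. It will be imprecise: with 21 preschools of about 9 children, the large-sample standard error at ICC 0.05 is (1 − 0.05)(1 + 8.1 × 0.05) × √(2/(9.1 × 8.1 × 20)) ≈ 0.05. It should therefore accompany the range, not replace it.

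The cost is a short recalculation and a restated paragraph, with no new data and no change to design or analysis. The downside is that the stated detectable differences may become larger, and the statement that they seem attainable would then need to be reconsidered.
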